### **SV1 - Safety evaluation after vaccine (7 /+ 2 days)**

- Evaluation of adverse events 7 days after the administration of standard dose vaccine (in person or by phone).

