### 3.3. Analysis populations

The following analysis populations will be defined for statistical analysis:

**Screened** – All patients screened for the study – having an acute coronary syndrome (ACS) during the hospitalization phase.

**Eligible but not randomized** – All screened patients who were eligible but not randomized due to the inclusion/exclusion criteria of the study.

**Intention to treat (ITT)** – All eligible patients who received a randomization number, and analyzed according to the group to which they were assigned, regardless of receiving the vaccine or not.

**Per Protocol (PP)** – All ITT patients who did not have major protocol violation. A protocol violation means a patient who was randomized but was not eligible (had not inclusion criteria or had at least one exclusion criterion); a patient who was treated with an immunization different from the one the patient was randomly assigned (e.g., intervention arm being

[figure not shown]

vaccinated after discharge). Patients vaccinated out of the window in the control arm due to the COVID-19 pandemic will still be included in the PP population, but a sensitivity analysis will be done excluding those patients as well (modified PP).

**Modified PP** –Due to the COVID-19 pandemic, some patients from the control group were not vaccinated within the expected study window or were vaccinated with a vaccine other than the study vaccination. Therefore, a modified PP population excluded these patients, as well as those ones that were not vaccinated at all (except for deaths occurred before vaccine could be administered)

**Safety** - All patients who received the vaccine. Patients who were vaccinated out of window or with vaccines other than study immunization (e.g., from an outpatient clinic) due to the COVID-19 pandemic were included in this analysis. Patients were analyzed according to the vaccination arm received, regardless of the randomized arm.

To avoid bias, if a patient had entered into study more than once, and in all these entries, this patient was considered eligible (i.e. met all inclusion/exclusion criteria), only the “first” enrollment will be maintained at the “Eligible patient population”, and the other(s) were excluded, due to duplicity.

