The primary efficacy analysis of the study comprises the ITT population. Safety analysis was made for the Safety population. Efficacy endpoints were performed in the PP and modified PP populations, and safety endpoints in the ITT population, as sensitivity analyses.

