#### Safety outcomes:

- Number and percent of unexpected serious adverse events (event that presents immediate risk to life, persistent or significant disability, requiring or prolonging the hospitalization, resulting in congenital anomaly, Guillian Barré syndrome, anaphylactic vaccination reaction, Peripheral Facial Paralysis, encephalitis or myelitis, optic neuritis, Stevens-Johnson syndrome, toxic epidermal necrolysis, anaphylactic vaccination reaction, another unexpected event judged as serious).
- Local and systemic adverse events after vaccination.
- Use of other vaccine than those available in the study (Hepatitis, Trivalent Influenza (Government), Pneumococcal, Yellow fever, Viral triple, DPT Adult, HPV).

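### The main Safety set includes patients given only a non-study vaccine, assigns them to no defined arm, and no planned safety analysis isolates the study vaccine

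*Combined protocol and SAP*

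**What the plan says.** SAP 3.3 (Analysis populations) opens the Safety definition with "All patients who received the vaccine". It then extends the set to patients immunised late or elsewhere: "with vaccines other than study immunization (e.g., from an outpatient clinic) due to the COVID-19 pandemic were included in this analysis". The grouping rule is "Patients were analyzed according to the vaccination arm received, regardless of the randomized arm". No sentence says which arm a non-study vaccine belongs to.

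The same section assigns the sets to analyses. For the main analysis, "Safety analysis was made for the Safety population". The only alternative for safety is "safety endpoints in the ITT population, as sensitivity analyses". The set that removes control patients given another vaccine, the modified per-protocol set, goes elsewhere: "Efficacy endpoints were performed in the PP and modified PP populations".

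The modified per-protocol definition confirms that some control patients did receive a vaccine other than the study's, without giving a number.

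SAP 5.1 lists among the safety outcomes "Use of other vaccine than those available in the study (Hepatitis, Trivalent Influenza (Government), Pneumococcal" and further vaccines. SAP 5.2 plans to describe local and systemic events up to 7 days by group, with a 95% confidence interval for any vaccination adverse event. It states no between-arm test of reactions.

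**The concern.** An as-received safety set should say what each patient received. Here the label is a study arm, but some members had neither two study doses in hospital nor one study dose at about 30 days. The product can differ as well: protocol 3.6.1 describes the study vaccine as quadrivalent and the national campaign vaccine as trivalent, and SAP 5.1 names the government trivalent vaccine among those used outside the trial.

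At stake is the comparator for reactogenicity. A reader will set the double-dose reaction rate beside the standard-dose rate, and the standard-dose figure may not be that of the study vaccine. The plan treats outside vaccine as different enough to remove in an efficacy sensitivity analysis, but has no matching safety analysis.

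There is also a smaller circularity. A patient who enters the Safety set only through an outside vaccine has, by definition, the listed safety outcome of having used a vaccine other than the study's.

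**Working it through.** The documents state no reaction rate, no share given outside vaccine and no precision target for safety, so there is no plan figure to reproduce. The check has two parts.

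**1. Which planned safety analysis is limited to study vaccine? (SAP 3.3)**

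| Set | Outside-vaccine-only patients | Used for safety? |
|---|---|---|
| Safety | Kept, arm undefined | Yes, main |
| ITT | Kept, by assigned arm, with unvaccinated patients added | Yes, sensitivity |
| Modified per-protocol | Removed (controls) | No, efficacy only |

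None is.

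**2. What would pooling do to the standard-dose rate?**

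The undefined mapping allows at least two readings: counted as standard dose, or not assignable to either column. The first is likelier, because the patients described under the modified per-protocol set are controls, but it is an inference. Under it:

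- observed rate = (1 − f) × p_study + f × p_ext
- shift = observed rate − p_study = f × (p_ext − p_study)

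All inputs below are assumptions except 900 per arm (protocol 6.1, SAP 2.3), which is the planned enrolment and not the Safety-set size. Take p_study = 20% and a double-dose rate of 30%: a true difference of 10 points and a true ratio of 1.50. The standard error of the difference is √(0.20 × 0.80/900 + 0.30 × 0.70/900) = √(0.37/900) = 0.0203, or 2.03 points. Let p_ext run from 0 (nothing recorded, scored as no reaction) to 30% (1.5 times p_study).

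| f | Shift, p_ext = 0 | Shift, p_ext = 20% | Shift, p_ext = 30% | Observed ratio, double/standard |
|---|---|---|---|---|
| 1% | −0.2 points | 0 | +0.1 points | 1.49 to 1.52 |
| 5% | −1.0 (−0.49 SE) | 0 | +0.5 (+0.25 SE) | 1.46 to 1.58 |
| 10% | −2.0 (−0.99 SE) | 0 | +1.0 (+0.49 SE) | 1.43 to 1.67 |
| 20% | −4.0 (−1.97 SE) | 0 | +2.0 (+0.99 SE) | 1.36 to 1.88 |
| 30% | −6.0 (−2.96 SE) | 0 | +3.0 (+1.48 SE) | 1.30 to 2.14 |

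Example for f = 20%, p_ext = 0: 0.80 × 20% = 16%, a shift of −4.0 points, and 30/16 = 1.88. For p_ext = 30%: 0.80 × 20% + 0.20 × 30% = 22%, a shift of +2.0 points, and 30/22 = 1.36.

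The SE multiples only give scale; they are not evidence of harm, because no such test is planned. With f = 0 (study vaccine only) the ratio returns to 1.50. The middle column shows that mixing alone does no numerical damage when recorded rates agree.

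**The case against.** Counting everyone vaccinated is a recognised, inclusive choice, and the SAP discloses it. Reactions are exploratory and only described. The stated objective (protocol 2.3) is the adverse-event rate of the double dose, which is untouched if outside-vaccine patients are counted as standard dose. Use of other vaccines is tabulated, so the mixture is visible, and the ITT repeat groups by assignment.

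A reader might go further and infer that short local reactions after an outside vaccine go unrecorded, so that the standard-dose rate is diluted and the double dose looks more reactogenic than it is. The documents do not support that:

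- Protocol 3.5 has all patients assessed at days 7 and 28 after vaccination, and SAP 2.5 has all assessed for seven days after the vaccination date.
- The control-arm contact, "Evaluation of adverse events 7 days after the administration of standard dose vaccine (in person or by phone", is tied to giving the standard-dose vaccine. That leaves the procedure for a dose given elsewhere unstated, but does not show that reactions are missed.
- The SAP's missing-data section leaves patients with missing categorical data out of percentages unless otherwise specified. Uncaptured reactions set to missing would therefore not be scored as absent.
- Protocol 3.6.1 describes the study and campaign vaccines as similar apart from one added B strain. No passage gives different reaction rates.

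These arguments remove any claim about direction or established distortion and reduce the weight of the point. They do not supply an arm for a non-study vaccine or a study-vaccine-only safety table. Tabulating outside use shows how many patients are mixed in; it does not separate their reactions.

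**Conclusion.** The point stands as a minor analysis-set defect. The main safety set pools patients who received neither study regimen under a study-arm label, the mapping is undefined, and no planned safety analysis isolates the study vaccine.

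The numerical effect cannot be fixed. It depends on f and on p_ext − p_study, neither of which the documents give. Under the assumptions above it runs from negligible at a 1% share, through −1.0 to +0.5 points at 5%, to −4.0 to +2.0 points at 20%, and is zero if recorded rates are equal. All of this assumes that outside-vaccine patients are counted as standard dose. It would be wrong to conclude that the contrast is distorted, or that the double dose is made to look worse.

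Patients who received the study vaccine late are a separate case: the product is unchanged. Nothing here concerns clinical management.

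**What to change.** In SAP 3.3 and 5.2:

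- Base the main reaction table on patients who received a study vaccine, in or out of window, grouped by study regimen received.
- Show patients given only a non-study influenza vaccine as a separate row.
- Pool them with the standard-dose group only in a labelled sensitivity analysis, with the mapping rule written down.
- Report use of other vaccines by randomised arm, so that entry to the set does not itself generate the outcome.

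The cost is a few lines of SAP text and one flag. Protocol 3.8.2 already requires other vaccines given during follow-up to be described in the eCRF. The standard-dose group in the main safety table becomes slightly smaller.

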## 4. TRIAL POPULATION

### 4.1. Screening data

The patient disposition tables will summarize the following:

1) For recruitment period and overall:

- The number of patients screened
- The number of patients who failed screening (non-eligible) - % calculated from the Screened population
- The number (%) of eligible patients into the study (% calculated from the Screened population) and the reasons for non-eligibility

2) For each randomization group and overall:

[figure not shown]

- The number (%) of randomized patients (ITT population) by site study
- The number (%) of randomized patients (ITT population) by site region and state
- The number (%) of patients in the different study populations (Eligible, Safety, ITT, PP and modified PP populations).
- The number (%) of patients who completed the study
- The number (%) of patients who withdrew from the study and associated reasons (% calculated from the Safety population)

The percentages will be calculated based on the number of randomized patients (ITT population), unless otherwise specified.

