**If the patient is randomized to double dose vaccine, it will be given during the hospitalization for the index event.**

Patients randomized to late standard dose influenza vaccine will receive it at the visit 30 days after randomization.

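### SAP 4.1 calculates withdrawal percentages by randomised group from the Safety population instead of ITT, so the base omits unvaccinated patients, mainly controls

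*Combined protocol and SAP*

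**What the plan says.** The second block of SAP 4.1 is headed "For each randomization group and overall". Its general rule on denominators is "The percentages will be calculated based on the number of randomized patients (ITT population), unless otherwise specified". The row for patients who completed the study states no base, so it takes that default. The next row is an express exception: "The number (%) of patients who withdrew from the study and associated reasons (% calculated from the Safety population").

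SAP 3.3 defines the two populations:

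- ITT is all eligible patients with a randomisation number, "analyzed according to the group to which they were assigned, regardless of receiving the vaccine or not".
- Safety is "All patients who received the vaccine". It keeps some patients who missed the scheduled study vaccine: "Patients who were vaccinated out of window or with vaccines other than study immunization" because of the pandemic are included. Its grouping rule is "Patients were analyzed according to the vaccination arm received, regardless of the randomized arm".

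Vaccination times differ by arm. Under SAP 2.1 the double dose is given during the hospital stay, as early as possible after randomisation. For the control arm, protocol 3.5.2 says "Patients randomized to late standard dose influenza vaccine will receive it at the visit 30 days after randomization"; the window is ±5 days.

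**The concern.** A withdrawal percentage shown by randomised group should describe everyone randomised to that group. Here the base depends on an event after randomisation, receipt of a vaccine, whose timing the design sets differently in the two arms. A control who withdraws or dies in the first month without any influenza vaccine is not in the base. The corresponding interval in the double-dose arm is usually much shorter.

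Two further problems follow from the wording. The table's columns are randomised groups, whereas Safety is organised by vaccine received, so a crossover has no clear column. And the SAP does not say whether the numerator is all withdrawals or only those among Safety patients. The completion row and the withdrawal row, one above the other, have different bases and cannot be reconciled.

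What is at stake is how follow-up loss is read in an open-label trial. SAP 2.3 makes win-ratio comparisons with a censored patient only up to censoring, and the SAP's Missing data section assumes that unobserved follow-up is missing at random. Readers judge that assumption partly by comparing loss between arms.

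**Working it through.** The plan states no withdrawal rate, so there is no figure to reproduce. The arithmetic shows how the row behaves under stated assumptions.

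**Inputs from the documents.** 900 patients per arm and a 12-month control death rate of 7.0% (SAP 2.3, protocol 6.1); control vaccination at 30 ± 5 days (SAP 2.1).

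**Assumptions.** 5% of controls withdraw before vaccination (range 1% to 10%) and 4% after; deaths occur at a constant hazard; controls who leave or die early have had no other influenza vaccine; all remaining controls are vaccinated; there are no crossovers.

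1. Control deaths before day 30: 1 − (1 − 0.07)^(30/365.25) = 0.59%, and 0.59% of 900 is about 5. Cut-offs at day 25 and day 35 give 4.5 and 6.2.
2. Withdrawals: 0.05 × 900 = 45 before vaccination and 0.04 × 900 = 36 after; total 81.
3. Controls in Safety: 900 − 45 − 5 = 850.
4. Control withdrawal percentage:
   - ITT base: 81/900 = 9.00%
   - (a) all withdrawals over Safety: 81/850 = 9.53%
   - (b) only Safety-set withdrawals over Safety: 36/850 = 4.24%
5. The same calculation over the range of early withdrawal:

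| Withdraw before vaccination | ITT base | (a) all / Safety | (b) Safety only / Safety |
|---|---|---|---|
| 1% | 45/900 = 5.00% | 45/886 = 5.08% | 36/886 = 4.06% |
| 2% | 54/900 = 6.00% | 54/877 = 6.16% | 36/877 = 4.10% |
| 5% | 81/900 = 9.00% | 81/850 = 9.53% | 36/850 = 4.24% |
| 10% | 126/900 = 14.00% | 126/805 = 15.65% | 36/805 = 4.47% |

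Reading (a) overstates control withdrawal by 0.08 to 1.65 percentage points. Reading (b) understates it by 0.94 to 9.53 points and hardly moves as early loss rises.

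6. Sensitivity to early deaths. SAP 2.3 notes that cardiovascular risk is highest early, so a constant hazard may give too few. If a third of the 0.07 × 900 = 63 expected deaths (21) fell before vaccination, Safety would be 900 − 45 − 21 = 834, giving (a) 81/834 = 9.71% and (b) 36/834 = 4.32%. The picture is the same.
7. Double-dose arm with the same 81 withdrawals. If everyone is vaccinated, the figure stays at 9.00%. If 1% (9 patients) withdraw unvaccinated, (a) is 81/891 = 9.09% and (b) is 72/891 = 8.08%. If 2% (18 patients) do, (a) is 81/882 = 9.18% and (b) is 63/882 = 7.14%. The distortion is smaller than in controls at 5% early control loss, but it is not zero. If no control withdrew early and 2% of the double-dose arm withdrew unvaccinated, the double-dose arm would be the more affected one.

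**The case against.** The strongest reply is that a reader can recover most of the picture elsewhere. The same table gives the number of withdrawals as well as the percentage, and the size of the ITT and Safety populations, by randomised group. On the plain reading of the numerator, the ITT percentage can therefore be recomputed. The completion row already uses ITT. SAP 4.3 shows loss to follow-up in the CONSORT diagram with reasons. SAP 4.4 tabulates losses by treatment group and lists reasons by patient. The Missing data section reports the fraction of subjects with unobserved follow-up, adds a pattern-mixture analysis, and places its impact analyses in ITT. All of this stands, and it limits the harm. The overlap is only partial: SAP 4.4 states no denominator, and the Missing data section does not say that its fractions will be given by arm.

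A reader might infer three stronger things that the documents do not support:

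- **The percentage is wrong in the control arm alone.** The double dose is also given after randomisation, so double-dose patients who leave or die unvaccinated are omitted too, and grouping by vaccine received can affect both columns.
- **Every control who misses the day-30 vaccine drops out of the base.** Controls vaccinated late or with another influenza vaccine because of the pandemic stay in Safety. SAP 3.2 expects vaccination outside the window, which is not withdrawal. SAP 3.3 does recognise patients never vaccinated, but gives no number.
- **The row conceals early control loss.** That needs reading (b). The row refers to patients who withdrew from the study, within each randomised group, which most naturally means all of them. On that reading the error is a modest overstatement.

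**Conclusion.** The row is wrong as written, and the point is minor. A percentage reported by randomised group is calculated on a vaccinated-only base that differs by arm, contradicts the section's own default and does not match the row above it. The distortion falls mainly, not exclusively, on the control arm. In the illustration, 9.0% becomes 9.5% on the plain reading of the numerator, or 4.2% on the narrower one. Both figures rest on assumed withdrawal rates and a constant death hazard, because the documents supply no withdrawal rate.

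A reader might also infer that the primary result is affected. It is not: SAP 3.3 sets the primary efficacy analysis in ITT, and no estimate, test, confidence interval or power figure uses this percentage. The error is confined to disposition reporting.

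**What to change.** In SAP 4.1, delete the Safety-population exception from the withdrawal row, so that the section's ITT default applies and withdrawal percentages and reasons are calculated by assigned arm. Use the same base for any percentages in SAP 4.4. The cost is one denominator in one table and a clarifying phrase in SAP 4.4; no new data are needed. Splitting withdrawals before and after the day-30 visit would show early control loss directly, but it is optional.

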## 4.2. Eligibility

### Inclusion Criteria:

- Men and women aged  $\geq 18$  years;
- Patients hospitalized with an acute coronary syndrome

### Exclusion Criteria:

- Participation in another clinical trial;
- Refusal to provide consent for the study;
- Hypersensitivity or anaphylaxis to any component of the vaccine;
- History of Guillain-Barré Syndrome within the six weeks after previous influenza vaccination;
- Have already received the influenza vaccine with the same strains used in the study within 12 months of inclusion in the study (it comprises trivalent or tetravalent vaccines with the same strains of the study);
- Pregnant women;
- Breastfeeding women;
- Presenting ACS between the months of December and February.
- Time from hospitalization for ACS  $> 7$  days.

[figure not shown]

### 4.3. Recruitment

A CONSORT flow diagram will be used to summarize the number of patients who were:

- Assessed for eligibility at screening
- Screened
- Ineligible at screening\*
- Eligible and randomized (ITT population)
- Eligible but not randomized\*
- Loss of follow-up\*
- Randomized and included in the primary analysis
- Randomized and excluded from the primary analysis\*

\*reasons will be provided.

### 4.4. Withdrawal/follow-up

The numbers of losses to follow-up (drop-outs and withdrawals) over the course of the trial will be summarized by treatment group using tables.

The reasons will be listed by patient and group.

### 4.5. Baseline patient characteristics

Patients will be described with respect to the type of ACS event at the time of selection (STEMI, NSTEMI or unstable angina), and demographic data (age, sex, race); lifestyle (smoking); medical history and comorbidities (arterial hypertension, dyslipidemia, diabetes, previous acute myocardial infarction, previous coronary angioplasty, previous surgical coronary revascularization, prior stroke, heart failure, creatinine clearance, history of hospitalization for influenza; and interventions performed for the index event before randomization (thrombolysis, percutaneous coronary intervention, myocardial revascularization surgery).

Continuous variables will be described by mean  $\pm$  standard deviation or median (interquartile range), according to distribution. Categorical and ordinal data will be summarized using the number and percentage of patients. Patients with missing data will not be included in calculations of percentages, unless otherwise specified. When relevant, the number of

[figure not shown]

patients with missing data will be presented. All baseline characteristics will be summarized overall and separately for the two randomized groups.

